# Efficacy and safety of Qushi Huayu granule for hyperlipidemia: study protocol for a randomized, double-blind, placebo-controlled trial

**DOI:** 10.1186/s13063-022-06031-3

**Published:** 2022-02-02

**Keywords:** Qushi Huayu granules, Hyperlipidemia, Traditional Chinese medicine, Randomized controlled trial

## Abstract

**Background:**

Hyperlipidemia has become a common chronic disease worldwide in recent years. Studies have shown that hyperlipidemia patients, especially those with a high level of serum low-density lipoprotein cholesterol (LDL-C), have a significantly higher prevalence of atherosclerosis, leading to coronary heart disease. Previous basic experiments and clinical studies have shown that Qushi Huayu granules (QSHY) reduce blood lipids in patients with non-alcoholic fatty liver disease (NAFLD) accompanied by hyperlipidemia. However, the clinical efficacy of QSHY in patients with hyperlipidemia is still lacking. This study aims to investigate the effect and safety of QSHY for hyperlipidemia.

**Methods:**

This is a randomized, double-blind, placebo-controlled trial. A total of 210 participants will be enrolled and randomized into the QSHY or placebo granules groups in equal proportions, who will receive treatment for 24 weeks. The primary outcome will be the change in LDL-C from baseline to week 12. Secondary outcomes will be changes in other serum lipids markers, life quality measuring health surveys, and traditional Chinese medicine (TCM) pattern scale. All related tests will be measured at baseline, week 12, and week 24 after enrollment. Adverse events and the safety of intervention will be monitored and evaluated.

**Discussion:**

We designed a clinical trial of hyperlipidemia management with QSHY, a TCM prescription. The results of this trial will present the efficacy and safety of QSHY in patients with hyperlipidemia.

**Trial registration:**

Chinese Clinical Trial Registry ChiCTR2000034125. Registered on June 25, 2019

## Administrative information

Note: the numbers in curly brackets in this protocol refer to SPIRIT checklist item numbers. The order of the items has been modified to group similar items (see http://www.equator-network.org/reporting-guidelines/spirit-2013-statement-defining-standard-protocol-items-for-clinical-trials/).

## Background

Due to the change of lifestyle and diet, the incidence rate of hyperlipidemia has increased significantly [1]. Fifty-three percent of adults, or more than 100 million people in the USA, have elevated levels of serum LDL-C [2]. The prevalence of dyslipidemia in Chinese adults is as high as 40.40% [3], and 45% of the prevalence is in Russia [4]. Hyperlipidemia usually refers to elevated serum cholesterol and/or triglyceride [5] levels due to the disorder of systemic lipids metabolism. Among them, the increase of LDL-C is the main risk factor of atherosclerosis [6, 7] leading to coronary artery disease, myocardial infarction(MI), and stroke [8, 9]. In addition, studies showed the relationship between the control of blood lipids and the progress of diseases such as osteoporosis [10], chronic kidney disease [11, 12], acute pancreatitis [13].

The treatment of hyperlipidemia is based on lifestyle change therapy, which is generally required to improve the diet structure and lifestyle, but has little effect on blood lipids level when used alone [14], further, cooperate with Western medicine, and start drug treatment according to the risk of atherosclerotic cardiovascular disease (ASCVD) [15, 16]. At present, statins in clinical application are used as the cornerstone of lipid-lowering medicines [17]. Other drugs and therapies, such as fibrates, ezetimibe, proprotein convertase subtilisin/kexin type 9 (PCSK9) inhibitors, bile acid sequestrants, niacin, and gene therapies, including gene therapy of small interfering RNA, antisense oligonucleotides, viral vector-mediated, and non-coding RNA therapy [18–20], are still in the laboratory research stage or have not been widely used in clinical. In clinical, the lipid-lowering drugs represented by statins have certain limitations, the incidence of adverse reactions of statins is relatively high [21, 22]. The main adverse reactions are gastrointestinal reactions, thrombocytopenia [23], liver and kidney function damage, myopathy, hyperglycemia, and neurotoxicity [24]. Myopathy is the most common adverse reaction. Rhabdomyolysis occurred in severe cases [25], and even statin-induced necrotizing autoimmune myopathy (SINAM) [26]. With the in-depth study of related research, several studies suggest that statins have a risk of diabetes [27].

Traditional Chinese medicine (TCM) has a good effect on hyperlipidemia [28]. In the 2002 version of the “Guiding Principles for Clinical Research of New Chinese Medicines,” hyperlipidemia is classified as the “phlegm” category of TCM. Phlegm-blood stasis are the main pathological products of hyperlipidemia; the phlegm and blood stasis is a common syndrome type of hyperlipidemia [29]. Although TCM prescriptions or certain herbal active ingredients show the effect of lowering blood lipids in some existing pre-clinical research reports, there are currently only a few Chinese patented final products with clear lipid-lowering application indications, such as Xuezhikang capsules [30], Zhibituo [31], and Zhibitai capsules [32] are on the market. Therefore, the treatment of hyperlipidemia by TCM lacks evidence-based medicine data support and market transformation.

Qushi Huayu (QSHY) is an empirical prescription of TCM, which consists of five herbs. QSHY has been proven to alleviate liver steatosis and inflammatory damage in patients with non-alcoholic fatty liver disease (NAFLD) and obese rodent models [33–36]. QSHY treatment significantly reduced the elevation of serum LDL-C, TC, TG, ALT, and AST in NAFLD rodent models induced by HFD [35, 37], the related mechanism is that QSHY could regulate the dysbiosis of intestinal microbiota and inhibit hepatic lipogenesis [37, 38]. Although the experimental evidence indicates that QSHY could be used in the administration of hyperlipidemia, there is still a lack of evaluation of the effect of QSHY in the treatment of patients with hyperlipidemia compared with placebo. Therefore, this study will investigate the efficacy and safety of QSHY for hyperlipidemia.

## Methods

### Study design

This study will investigate the efficacy and safety of QSHY as a treatment for hyperlipidemia diagnosed with phlegm-blood stasis syndrome. This is a randomized, double-blind, placebo-controlled trial. The flow diagram of this trial is shown in Fig. 1. This study will be conducted in Shuguang Hospital Affiliated to Shanghai University of Traditional Chinese Medicine.

**Fig. 1 Fig1:**
[figure not shown]
Flow diagram of this study protocol

### Participants

#### Inclusion criteria

The following are the inclusion criteria:
For patients who meet the diagnostic criteria of Chinese and Western medicine for hyperlipidemia. The diagnostic criteria for hyperlipidemia refer to the Chinese Guidelines for the Prevention and Treatment of Dyslipidemia in Adults (2016 Revised Edition) [39]. TCM diagnosis, syndrome differentiation criteria, and their basis refer to the TCM diagnosis and treatment criteria for dyslipidemia formulated by the heart disease branch of the Chinese society of TCM [40].Aged over 18 years.Participates without ASCVD, 3.4 mmol/L < LDL-C < 4.9 mmol/L; ASCVD patients, 2.6 mmol/L < LDL-C < 4.9 mmol/L.Patients with fasting TG < 5.7 mmol/L.BMI < 35 kg/m^2^.Willing and able to follow the scheduled visit plan, diet and exercise instructions, laboratory tests, and other procedures.Patients who signed informed consent.

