#### Exclusion criteria

The following are the exclusion criteria:
The patients who used other lipid-lowering drugs 4 weeks before enrollmentPatients with uncontrolled endocrine or metabolic diseases that may interfere with blood lipids levelsPatients taking oral corticosteroidsPatients with a history of alcohol or narcotic drug abuse within 1 year before screeningPatients with a high or very high risk of arteriosclerotic cardiovascular diseasePatients with congestive heart failure, unstable angina, MI, stroke, coronary artery bypass surgery or angioplasty, or unstable/serious peripheral artery disease in the past 6 monthsThose who have undergone gastrointestinal surgery in the past year or those who have taken weight-loss drugs in the past 3 months and have lost more than 10% of their body weightPregnant or lactating female patientsPatients with serious primary diseases or other major diseases such as malignant tumors

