### Interventions

Included participants in the treatment group will receive QSHY granules, while QSHY-simulated granules as placebo will be applied in the control group. Both groups of participants will receive regular health education, including diet control, exercise, and behavior modification. (1) Diet adjustment: diets with low sugar, low fat, and high vitamin will be recommended; (2) strengthen physical exercise: moderate metabolic equivalent exercise will be recommended for more than 30 min each time, 4 times a week; and (3) adjust emotion and keep a good mood.

The QSHY are compound preparations of 5 Chinese herbs, Artemisiae scopariae herba (Yin Chen), Polygoni cuspinati rhizome et radix (Hu Zhang), *Curcumae longae* rhizome (Jiang Huang), Gardeniae fructus (Zhi Zi), and Herba hyperici japonici (Tian Jihuang), packaged in consecutively numbered drug containers. The number was distributed according to the randomized number. The placebo will have an identically packaged appearance, weight, and taste compared to the QSHY granule. Both QSHY granule and placebos will be produced by Jiangyin Tianjiang Pharm Co. Ltd., Jiangsu, China. Participants will be advised to take one pack after meal, twice a day. The drugs are stored in the clinical trial base certified by Good Clinical Practice (GCP) and are managed and distributed in an independent clinical medicine center. The number of drugs received, taken, and returned by the patients will be recorded in detail by the research doctors at each visit. During the experimental period, non-pharmacologic care is permitted, but other TCM herbs and Western medication for lipid-lowering or fatty liver treatment will be prohibited.

Participants will be provided the information of the treatment and be advised not to take concomitant medications or change the dose and frequency of drugs autonomously. To facilitate completion, participants will be suggested to contact the arranged physicians for any questions raised about this trial. The drugs left over will be returned, and the related medication compliance will be calculated. Any combination of medications will be recorded in detail. Participants will be recommended to visit the outpatient clinic regularly for post-trial care.

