### Study visit overview

The visits in this trial are designed as 5-time points during 24 weeks of intervention: baseline, 6 weeks ± 5 days after enrollment, 12 weeks ± 5 days after enrollment, 18 weeks ± 5 days after enrollment, and 24 weeks ± 5 days after enrollment. At each visit time point, participants will be tested the laboratory index or recorded vital signs according to the study schedule. The detailed flow path information is shown in Fig. 2.

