## Discussion

Hyperlipidemia is a companion to many metabolic diseases, such as NAFLD and coronary heart disease. According to previous studies, QSHY can improve liver function and blood lipids, including TC, LDL-C, and TG of HFD rodent models [34], and no adverse reactions were found [35, 37]. Three previous clinical trials in China [33, 34, 43] have shown that QSHY significantly reduces ALT and AST in patients with NAFLD and can reduce serum TG and TC, which indicates that QSHY has a therapeutic effect on patients with NAFLD and hyperlipidemia. However, the data presented are all based on the inclusion criteria of NAFLD patients, and precise data of QSHY for hyperlipidemia is still lacking. We designed this protocol to explore whether QSHY is an effective treatment of hyperlipidemia.

We designed a randomized, double-blind, placebo-controlled clinical trial based on a superiority framework. Hyperlipidemia can be improved by diet control and regular exercise. in this study, we include participants with mild to moderate abnormalities in LDL value and strengthened health education for the subjects. We excluded patients who must undergo lipid-lowering therapy, such as those who are at high or very high risk of ASCVD, or had unstable or severe arterial disease events 6 months before screening, to avoid violating ethical requirements. Therefore, we chose placebo as a comparator. The use of placebo control can clarify the absolute efficacy of the study drug and have higher efficiency.

A high level of LDL-C, not only a biomarker, appears to be a causal factor of the pathophysiology of ASCVD. According to the guidelines for the management of dyslipidemias issued by the European Society of Cardiology/European Atherosclerosis Society (ESC/EAS) in 2019 [44], serum LDL-C level is recommended as the main outcome for screening, diagnosis, and management of lipid modification to reduce cardiovascular risk. Thus, we set LDL-C, not TC or TG, as the primary outcome in this trial. According to the 2002 guiding principles of clinical research on new drugs of traditional Chinese medicine, participants are recruited according to the conventional TCM syndrome identification before randomization.

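### The LDL-C entry window for ASCVD patients does not fit the exclusion of high ASCVD risk and the placebo rationale: it is either a dead clause or lets stable ASCVD patients be randomised to placebo

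*Protocol article*

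**What the plan says.** Four parts of the protocol article bear on this point.

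- **Inclusion criteria.** Participants without ASCVD need LDL-C above 3.4 and below 4.9 mmol/L. A second, lower window follows: "ASCVD patients, 2.6 mmol/L < LDL-C < 4.9 mmol/L".
- **Exclusion criteria.** Patients "with a high or very high risk of arteriosclerotic cardiovascular" disease are excluded. A separate item, with a look-back counted in months, lists heart failure and also "unstable angina, MI, stroke, coronary artery bypass surgery or angioplasty, or unstable/serious peripheral artery disease in the past 6". A third reads "The patients who used other lipid-lowering drugs 4 weeks before" enrolment. The article does not define the risk classes or say whether established ASCVD belongs to them.
- **Interventions and Study visit overview.** During the trial "Western medication for lipid-lowering or fatty liver treatment will be prohibited". On duration: "The visits in this trial are designed as 5-time points during 24 weeks of intervention".
- **Discussion.** The choice of placebo rests on these exclusions: "We excluded patients who must undergo lipid-lowering therapy, such as those who are at high or very high risk of ASCVD". A recent unstable or severe arterial event is the second example given, and placebo is then presented as the comparator that these exclusions make ethically acceptable.

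**The concern.** The inclusion list invites in a group with the disease, and the exclusion list turns away people at high risk of the same disease. The placebo argument then leans on the exclusion and does not mention the group that was invited in.

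Two things are at stake. A screener with a stable ASCVD patient has two rules that can point in opposite directions and no stated way to rank them. And if the window is meant to operate, the trial can withhold lipid-lowering drugs for 24 weeks from people who have the disease, while its own ethical argument treats people at high risk of it as needing those drugs.

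**Working it through.** The plan gives no figure for this point, so the check sets the rules side by side.

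**1. What the window does.** Without ASCVD the LDL-C range is 3.4 to 4.9 mmol/L; with ASCVD it is 2.6 to 4.9 mmol/L. The extra band is 3.4 − 2.6 = 0.8 mmol/L wide and is open only to ASCVD patients. The clause therefore has a purpose only if some ASCVD patients can enter.

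**2. First reading: established ASCVD counts as high or very high risk.** The exclusion then removes everyone the window would admit, and the inclusion list describes a group that cannot enter. Excluding ASCVD under the item on serious or major diseases would have the same effect.

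**3. Second reading: established ASCVD does not count.** Take a patient with stable ASCVD, LDL-C inside the window, none of the listed events in the past 6 months, and no other lipid-lowering drug in the 4 weeks before enrolment. If the remaining criteria are met, nothing listed keeps this patient out. Allocation is 1:1, so the chance of placebo is one half. Both arms receive health education, but other lipid-lowering drugs are barred for the 24 weeks.

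**4. Second reading against the placebo rationale.** The Discussion says that patients who must have lipid-lowering therapy were excluded and gives two examples: the high-risk classes, and unstable or severe arterial events in the preceding 6 months. The patient in step 3 is in neither. The general principle has no matching item in the exclusion list, so a screener cannot apply it directly. Someone at high risk is thus excluded as needing treatment, while someone with the disease may be given placebo. The article itself says in the Background that drug treatment starts according to ASCVD risk, and its inclusion criteria set a lower LDL-C threshold for ASCVD patients.

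**5. Would a definition of the risk classes resolve this?** It would select step 2 or step 3. Under step 2 the inclusion item still needs correcting; under step 3 the rationale still needs completing.

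**6. Size.** Let k be the number who enter through the ASCVD window. The documents do not give k. On the first reading, with the exclusion applied, k = 0. On the second, about k/2 would be on placebo. The Trial status section reports 102 enrolled of a planned 210, so 210 − 102 = 108 places were still open. That is how many entrants a clarified rule could govern, not a measure of how many have ASCVD. The sample size of 105 per group does not use ASCVD status and is unaffected.

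**The case against.** The strongest defence is that no outright contradiction is shown. The lower threshold, and an event exclusion limited to 6 months, both suggest that stable ASCVD was meant to be eligible. Risk of a disease can be read as applying only to people who do not yet have it. On that reading the eligibility rules fit together. The Discussion states a general principle and offers its two groups only as examples. The risk classes may be defined in the full protocol, which is not shown, and their absence from an article is no fault. Ethics approval is recorded, and participants may withdraw at any time.

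Much of this stands. The article does not prove that the criteria conflict, and the hints do favour the second reading without settling it. The missing definition is not the point made here. What remains is that three published statements do not fit together on either reading, and the reading under which eligibility is coherent is the one under which the placebo argument fails to cover an admitted group.

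A reader might go further and infer that patients who need treatment are being denied it, or that ASCVD is by definition very high risk and the window is therefore an error. The documents support neither. Both depend on clinical guidance outside them, and no ASCVD patient is shown to have been enrolled. Nor do the documents show any effect on the primary comparison.

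**Conclusion.** The point holds as an inconsistency between the inclusion item, the exclusion item and the placebo rationale. On the first reading the harm is small: a clause that can mislead screening. On the second it is an ethical gap: stable ASCVD patients on placebo for 24 weeks under a rationale that excludes people at lesser disease stages. The number of patients affected is unknown and may be zero.

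The conclusion assumes only that the published criteria are the ones in force. It does not depend on how any guideline ranks established ASCVD.

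A side consequence is conditional. The Statistical analysis section limits the full analysis set to participants who satisfied the entry criteria. That is a general feature of the plan, and it touches ASCVD patients only if someone already randomised is later ruled ineligible. It adds little weight here but should be closed off when the criteria change.

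**What to change.** **Preferred.** Reduce the inclusion item to one window for everyone, LDL-C above 3.4 and below 4.9 mmol/L, and add established ASCVD to the exclusions. This follows the protocol's own argument for placebo.

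**Alternative,** if the sponsor and the ethics committee intend to keep stable ASCVD: exempt it by name from the high-risk exclusion, and add to the Discussion a justification of placebo for these patients.

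**In either case,** check the records of the patients already enrolled (102 at the time of the article) for entry through the ASCVD window, and report the count to the ethics committee. State in the Statistical analysis section that any such patient already randomised stays in the full analysis set.

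**Cost.** An amendment with ethics reapproval, which the Ethics issue section already requires for any revision, and a record check at one centre. Under the preferred fix the eligible pool is unchanged on the first reading and smaller on the second, by an amount that cannot be estimated because the documents give no ASCVD share. The total of 210 and the planned t-test or Mann-Whitney comparison do not change.

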#### Exclusion criteria

The following are the exclusion criteria:
The patients who used other lipid-lowering drugs 4 weeks before enrollmentPatients with uncontrolled endocrine or metabolic diseases that may interfere with blood lipids levelsPatients taking oral corticosteroidsPatients with a history of alcohol or narcotic drug abuse within 1 year before screeningPatients with a high or very high risk of arteriosclerotic cardiovascular diseasePatients with congestive heart failure, unstable angina, MI, stroke, coronary artery bypass surgery or angioplasty, or unstable/serious peripheral artery disease in the past 6 monthsThose who have undergone gastrointestinal surgery in the past year or those who have taken weight-loss drugs in the past 3 months and have lost more than 10% of their body weightPregnant or lactating female patientsPatients with serious primary diseases or other major diseases such as malignant tumors

### Randomization and allocation

The consecutive random sequence of 2 groups is provided by the clinical medicine center with SAS version 9.1 statistical software. Eligible participants will be randomly allocated into the QSHY group or the placebo group in a 1:1 ratio. The random sequence will be sealed in opaque envelopes and locked in the independent clinical medicine center. The allocation concealment will be maintained until all the data of each participant in each visit had been uploaded and locked.

### Blinding

#### Blind editing and blind bottom preservation

All patients and researchers will be blinded to the treatment assignments until the trial is completed. Personnel unrelated to this clinical trial will complete the preparation of drug blinding and emergency letters. Duplicate blinding is adopted in this study. All the data will be uploaded into the electronic database in double copies; the final statistical plan will be confirmed by question answering, verification, and blind review; and the database will be locked. After that, the first unblinding will be performed, and the results of the undefined group information corresponding to random numbers for necessary statistical analysis can be obtained. After the analysis, the main researcher will perform the second unblinding with the identification of two groups. All the unblinding processes will be recorded. In case of emergency, the reason, time, and place of blindness breaking will be recorded, and the cases will be treated as missing cases.

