### Outcomes

The primary outcome in this study is the change in LDL-C from baseline to week 12. The secondary outcomes are the changes in fasting serum TC, TG, HDL-C, non-HDL-C, apolipoprotein (Apo) A-I, ApoA-II, ApoB, and fasting blood glucose at 12-week assessment and 24-week assessment, and the change in the ratio of TC/HDL-C at 12-week assessment and 24-week assessment. All mentioned serum biochemical markers will be measured at baseline, 12-week, and 24-week after randomization. The measurement of life quality will be assessed by the Medical Outcomes Study Item short-Form Health Survey (SF-36) questionnaire. The changes in the syndrome of TCM for participants will be measured using four TCM diagnostic methods and the Scores of TCM syndrome Scale. Other outcomes are blood pressure, heart rate, body mass index (BMI), and waist-to-hip ratio (WHR).

Safety indexes are blood and urine routine examination and results of serum liver function test including AST, ALT, alkaline phosphatase (ALP), and serum renal function test including creatinine (CR) uric acid (UA) and blood urea nitrogen (BUN). Adverse events that occurred in the trial period will be monitored at each visit. All collected adverse events and their degree will be recorded with followed medical intervention in the CRF.

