### Statistical analysis

The statistical analysis will be performed by an independent statistician. After the trial protocol is determined, the statistician is responsible for formulating the detailed statistical analysis plan in consultation with the principal investigator. Statistical analysis will be conducted using the SAS version 9.1 statistical software.

The primary analyses for this study will adopt the intention-to-treat (ITT) principle. The full analysis set [41] includes participants who met the inclusion and exclusion criteria and received at least one evaluation after randomization. The per-protocol set (PPS) includes participants who had good compliance (80–120% of the trial drugs were used), did not take prohibited drugs during the trial, and completed the CRF. Safety analysis will be conducted based on a safety analysis set including participants who have received at least one intervention and safety evaluation.

Participants can withdraw at any time and will be recorded the reason for withdrawal. Participants who discontinue or deviate from intervention protocols will be informed by interviewers to get the reason for dropout. The original data of all withdrawn and terminated cases should be kept and recorded for further analysis. The last observation of participants who dropped out or existing missing data will be carried forward as the final data.

Continuous variables will be presented as mean ± standard deviation [42] or median with quartile range, according to the distribution. An independent *t*-test or the Mann-Whitney *U* test will be conducted to compare the differences between the groups. Dichotomous variables will be presented as frequency and percentage and analyzed with the chi-square test or Fisher’s exact test. Subgroup analyses will be performed based on groups with high heterogeneity if necessary.

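### Treating emergency-unblinded participants as missing conflicts with the stated ITT analysis and, under LOCF, can replace an observed week-12 LDL-C with the baseline value

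*Protocol article*

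**What the plan says.** The protocol article's Blinding section (Blind editing and blind bottom preservation) sets the rule for an emergency code break: "In case of emergency, the reason, time, and place of blindness breaking will be recorded, and the cases will be treated as missing cases". It makes no distinction by timing of the break or by type of data.

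The Statistical analysis section states the principle: "The primary analyses for this study will adopt the intention-to-treat (ITT) principle". The full analysis set (FAS) that follows "includes participants who met the inclusion and exclusion criteria and received at least one evaluation after randomization". Missing data have a single rule: "The last observation of participants who dropped out or existing missing data will be carried forward as the final data".

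The Outcomes section names the change in LDL-C from baseline to week 12 as primary and fixes the sampling times: "All mentioned serum biochemical markers will be measured at baseline, 12-week, and 24-week after randomization".

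Safety has its own population: "Safety analysis will be conducted based on a safety analysis set including participants who have received at least one intervention and safety evaluation".

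**The concern.** An emergency code break is a post-randomisation event. It will usually follow a clinical problem, and that problem may be related to the treatment received. Setting a participant's data aside for that reason is what an ITT analysis is meant to prevent.

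The protocol also does not say what becomes of a case treated as missing. It may stay in the analysis with a carried-forward value, or it may leave the analysis. Both readings discard a week-12 LDL-C that may have been measured, and they can move the estimate in opposite directions. The choice would fall to the analyst, in the primary analysis.

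**Working it through.** **Inputs.** Lipid sampling at baseline, week 12 and week 24 (Outcomes). LOCF for dropouts and missing data (Statistical analysis). Proportions 0.305 and 0.155, α = 0.05, β = 0.2, 94 per group, 105 after a 10% loss (Sample size). The rate of emergency unblinding is not given. I assume that a share u of an arm is unblinded before week 12 and show u from 1% to 10%.

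**The plan's own figure.** The plan gives no figure on code breaks. Its sample size is reproduced because it is used below. The printed formula, with z(0.95) = 1.645 and z(0.80) = 0.842, gives

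n = (1.645 + 0.842)² × (0.305 × 0.695 + 0.155 × 0.845) / 0.15² = 94.24,

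against the stated 94. Then 94 / 0.9 = 104.4, hence 105.

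**Reading A: missing, then LOCF.** The only lipid value before week 12 is the baseline one. A participant unblinded before week 12 is therefore given baseline LDL-C, a change of exactly zero, whether or not a week-12 sample was taken. If the others in the arm have mean change m, the analysed mean is

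(1 − u) × m + u × 0 = (1 − u) × m.

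With different shares in the two arms, the analysed difference is (1 − u_T) × m_T − (1 − u_C) × m_C. Breaks on active treatment shrink that arm's apparent change, and breaks on placebo shrink the placebo change.

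**Reading B: missing, then excluded.** The analysed mean is m. If the excluded participants truly had zero change, the true arm mean is (1 − u) × m, so the analysed mean is too large by the factor 1 / (1 − u). The analysed set is then no longer ITT. If the losses come on top of the planned 10% in both arms, n per arm = 105 × (0.90 − u). On the protocol's own one-sided basis,

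power = Φ(0.15 / √(0.34295 / n) − 1.645), where 0.34295 = 0.305 × 0.695 + 0.155 × 0.845.

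| u (assumed) | A: mean multiplied by | B: mean inflated by | B: n per arm | B: power |
|---|---|---|---|---|
| 0 | 1.00 | 1.000 | 94.5 | 80.1% |
| 1% | 0.99 | 1.010 | 93.45 | 79.7% |
| 2% | 0.98 | 1.020 | 92.4 | 79.3% |
| 5% | 0.95 | 1.053 | 89.25 | 78.1% |
| 10% | 0.90 | 1.111 | 84.0 | 75.9% |

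The power column is indicative only, since the sample-size formula compares proportions and the primary outcome is a change in LDL-C.

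**Comparing the readings.** Reading A gives the right mean only if unblinded participants truly have zero change. Reading B gives it only if they change like the others. Neither assumption is needed where the week-12 value has been measured.

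**The FAS.** It requires confirmed eligibility and a post-randomisation assessment, so it is not all randomised participants. That makes it a modified-ITT set, and the protocol does not say how it relates to the ITT statement just before it.

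**The case against.** **Missing need not mean removed.** The LOCF rule would keep such a case in the FAS. If LOCF carries the last value before the break, a break after week 12 leaves the primary endpoint intact. This stands. It limits the LOCF harm to breaks before week 12 in participants who still give a week-12 sample. It also means that one case cannot both leave the efficacy set and carry an imputed value, so the two readings are alternatives and not cumulative.

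**Unblinding can affect LDL-C.** The assay is objective, but a participant who learns the allocation may change diet or exercise or take another lipid-lowering drug. The Discussion concedes that lifestyle interference cannot be eliminated. This is fair, and the case here does not rest on LDL-C being immune to unblinding. But it does not justify substituting the baseline value. ITT accepts what follows randomisation, and a per-protocol analysis is the place to set such participants aside.

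**The FAS restriction is common.** True, and only eligible participants are to be randomised, so few should be lost this way. It is a labelling point.

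**Safety.** A reader might infer that code-broken cases also disappear from the safety comparison. The documents do not support that. The safety set has its own definition with no exclusion for a broken blind. The Outcomes section says "All collected adverse events and their degree will be recorded with followed medical intervention in the CRF", and the Statistical analysis section says "The original data of all withdrawn and terminated cases should be kept and recorded for further analysis". Because the blinding rule speaks of cases without qualification, a clarifying clause is useful, but no loss of safety data is shown.

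**Conclusion.** The point holds for the primary efficacy analysis. The blinding section states a rule, so this is not a detail left to a later analysis plan, and no such plan could follow both that rule and the ITT principle. Under LOCF the rule can overwrite a real week-12 LDL-C with a change of zero. Under exclusion the set is not ITT.

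The size is modest. At an assumed 1% to 10% of an arm unblinded before week 12, LOCF multiplies that arm's mean change by 0.99 to 0.90, and exclusion inflates it by 1.010 to 1.111 if the true change was zero. On the protocol's own power basis, exclusion costs 0.4 points at 1% (80.1 − 79.7) and 4.2 points at 10% (80.1 − 75.9). All of this rests on assumed rates. If code breaks are rare, the numerical effect is slight, and the reason to act is possible treatment-related bias and the contradiction in the text.

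The FAS label is a secondary matter of wording.

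**What to change.** In the Blinding section, replace the treatment of code-broken cases as missing with a statement to this effect: participants whose blind is broken in an emergency stay in the primary analysis set in their assigned arm, with all LDL-C values observed before and after the break; any exclusion for a broken blind applies to the per-protocol set only; and they remain in the safety set as the Statistical analysis section already defines it. This concerns the handling of data only and says nothing about treatment after a code break.

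In the Statistical analysis section, label the FAS as a modified-ITT set.

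No measurements beyond the scheduled visits are required. The cost is a short protocol amendment. The Ethics issue section requires ethics reapproval of any revision, with researchers and already enrolled participants informed. Trial status reports 102 of the planned 210 enrolled and recruitment still open, so the change can be made before database lock and the first unblinding.
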